### **3.8.2.2. Face Validity**

The health education intervention will be translated to Malay language and pre-tested among young people to assess their understanding and face validity. The face validity will be measured by asking about the materials, the delivery of health education and if there is any improvement or changes that should be made. All of the comments and feedback will be taken and the amendment will be done accordingly.

### **3.9 Data Collection**

Data will be collected using pre-tested questionnaires. Evaluations will be made at three-time points, once at baseline after consent is taken from participants, following the two weeks after the intervention and at one month follow up. Prior to the commencement of the intervention, a baseline pre-test assessment will be conducted to identify participant's sociodemographic status and mental health literacy. Then the mental health literacy questionnaire will be evaluated post intervention and at follow-up. They will then measure and compared.

### **3.10 Data Analysis**

#### **3.10.1 Descriptive Analysis**

Data will be analysed using the IBM Statistical Package for Social Science (SPSS) version 25. Descriptive statistics will be used to describe the baseline characteristics of respondents. Data will be analysed according to intention to treat analysis. Mean and standard deviation will be used for continuous data, the median and interquartile range for not-normally distributed continuous data, and percentage for categorical data. The normality of the data will be check using histogram, Kolmogorov-Smirnov, and Shapiro-Wilk normality test.

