### **3.4.7 Randomization**

Participants who have given consent will be given a unique id number. They will then randomly be allocated to the intervention or control group using their id number. A randomized block design with a block size of four will be used, with the allocation of participants to the group established before the study commenced (Kendall JM, 2003). The randomization will be done by a person who is not a part of the research team, to ensure allocation concealment.

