### **3.4.9 Sample Size**

The sample size ( $n_1$ ) for this study was calculated by using the two population mean formula for hypothesis testing (Lemeshow et al., 1990). The sample size calculated was based on the mean Mental Health Literacy Score before and after the intervention. The summary of the sample size calculation is shown in Table 1.

$$N1 = \frac{2SD^2 (z(1-\alpha/2) + z(1-\beta))^2}{(\mu1-\mu2)^2}$$

Where,

N = sample size estimate

S = pooled standard deviation

$Z_{1-\alpha/2}$  = 1.96 (confidence level of 95%,  $\alpha$  is 0.05)

$Z_{1-\beta}$  = 0.84 (power of 80%,  $\beta$  is 0.2)

$\mu1-\mu2$  = estimated mean difference of two groups

$S^2$  = pooled standard deviation. This is calculated according to IUPAC (IUPAC, 2006) criteria given the equation;

$$S_P = \frac{(n_1-1)s_1^2 + (n_2-1)s_2^2 + \dots + (n_k-1)s_k^2}{n_1 + n_2 + n_3 + \dots + n_k - k}$$

Where;

$S_p$  is the Pooled Standard deviation

$n_1$  = number of participants in the control group

$n_2$  = number of participants in the intervention group

$s_1$  = standard deviation of mental health knowledge in the control group

$s_2$  = standard deviation of mental health knowledge in the intervention group

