**Table 3.1 Summary of Sample Size Calculation**

| Reference
s                     | Mean (sd)
interventi
on group | N
interventi
on group | Mean
control
group | N control
group | Sp   | n1 |
|------------------------------------|-------------------------------------|-----------------------------|--------------------------|--------------------|------|----|
| Campos
et al.,
2018 | 75.91
(8.13)                     | 239                         | 69.02
(8.23)          | 263                | 8.18 | 44 |

The total sample size in ( $n_1$ ) in this study is 88 (44 participants per arm). After considering 50% loss to follow up, a final sample size of 132 (66 participants per arm) was determined to be sufficient for this study.

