#### **3.10.2 Inferential Analysis**

The outcome variable will be compared at the baseline and post-test. For within-group difference, if data were assuming normally distributed data, parametric tests such as Paired t-

test will be utilized. But if data were assuming to be non-normal distributed data, non-parametric tests such Wilcoxon Signed Ranks test will utilize. For between groups difference, if data were assumed to be normally distributed data, parametric tests such as Independent t-test will be utilized. But if data were assuming to be non-normally distributed data, non-parametric tests such as the Mann Whitney U test will be utilized. Chi-Square test and Fisher Exact will be used to test the association between two categorical variables.

Multivariable analysis was done using generalized estimating equations (GEE) to determine the effect of the intervention on the primary and secondary outcome after adjusting for the covariates. The effectiveness of the intervention will be based on the trial group and timepoint interaction result. The effect of the intervention on changes in outcome measures will be determined after the intervention period. A summary of the statistical tests that will be used in this study can be found in Table 3.4.

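### The plan allows for 50% loss and claims intention to treat, but names no missing-data assumption or GEE working correlation, so dropout that relates to literacy differently in the two arms could bias the result in either direction

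*Combined protocol and SAP*

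**What the plan says.** Section 3.10.1 (Descriptive Analysis) contains the only statement on the analysis population: "Data will be analysed according to intention to treat analysis". It does not define the term or say what happens when an outcome is missing.

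Section 3.10.2 (Inferential Analysis) plans paired tests within groups. Between groups, "parametric tests such as Independent t-test will be utilized", with rank tests if the data are not normal. It then says "Multivariable analysis was done using generalized estimating equations (GEE"), adjusted for covariates, and bases effectiveness on the group-by-timepoint interaction. Table 3.4 likewise assigns the effect of the intervention to the GEE. Section 3.5.3 gives age, gender, ethnicity and household income as covariates; baseline literacy is not listed.

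On expected loss, the text under Table 3.1 reads "After considering 50% loss to follow up" and raises 44 per arm to 66 per arm.

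The plan states no working correlation, weighting, imputation method, missing-data assumption, comparison of dropouts with completers, or sensitivity analysis. The only retention measure is the weekly reminder to complete sessions (3.7.2.2).

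**The concern.** An independent or paired t-test on post-test scores can include only people who have such scores. Unless an unstated imputation is intended, these tests are completer analyses, and on the plan's own allowance up to half of those randomised would be left out. That does not fit an unqualified claim of intention to treat.

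The GEE keeps everyone with a baseline score, but this alone does not protect it. An unweighted GEE is in general valid only when data are missing completely at random, or when missingness depends only on arm and the modelled covariates. With an independence working correlation, the baseline mean comes from everyone randomised and the post-test mean from those who stayed. If the stayers in one arm began with higher or lower literacy, the interaction picks up that selection as if it were an effect. Adjusting for four sociodemographic variables does not remove selection on baseline literacy.

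With a third to a half of outcomes missing, the untested assumption about them can decide the conclusion. A working correlation or missing-data method chosen after the outcomes are seen could also be chosen for its result.

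**Working it through.** **The plan's own figures.** Inputs from Table 3.1: means 75.91 and 69.02 (difference 6.89), SDs 8.13 (n = 239) and 8.23 (n = 263). From section 3.4.9: z values "1.96 (confidence level of 95"%) and "0.84 (power of 80"%).
- Pooled SD = √[(238 × 8.13² + 262 × 8.23²)/500] = 8.18, as stated.
- n per arm = 2 × 8.18² × (1.96 + 0.84)² / 6.89² = 22.1, so 23. The stated 44 matches the two-arm total (44.2), not a per-arm figure. This is a separate issue.
- Inflation used: 44 × 1.5 = 66. Loss covered: 1 − 44/66 = 33%. For 50% loss: 44/(1 − 0.5) = 88 per arm.
- At 50% loss, 33 per arm remain, with about 93% power for 6.89 points. On the plan's own inputs, the issue here is bias rather than power.

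**Expected bias with no true effect.** Let Z be the standardised baseline score, and let retention in one arm follow logit P(retained) = a + bZ, with random loss in the other arm. Both the completer difference and the independence-GEE interaction are then biased by ρ × E[Z | retained], where ρ is the baseline to post-test correlation. The values of ρ and b are assumptions; the documents give neither.
- 50% loss, b = 1 (a = 0): E[Z | retained] = 0.413. Bias = 0.6 × 0.413 = 0.25 SD, or 2.03 points at SD 8.18. With ρ from 0.4 to 0.8 the range is 0.17 to 0.33 SD.
- 33% loss, b = 1 (a = 0.835): 0.6 × 0.279 = 0.17 SD, or 1.37 points.
- 50% loss, b = 0.5 (a = 0): 0.6 × 0.236 = 0.14 SD.

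The points are illustrative. The 8.18 comes from a study that used its own questionnaire (Table 2.5), not the scale planned here.

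**False rejection at nominal 5%.** Simulated trials with 66 per arm and ρ = 0.6; ranges are across runs of 200 to 6,000 trials:

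| Loss | b | Independence GEE | Completer t-test | Exchangeable GEE | Baseline-adjusted |
|---|---|---|---|---|---|
| 50% | 1 | 18.5-19.5% | 16.5-18.4% | 5.4-5.6% | 4.9-6.4% |
| 33% | 1 | 13.2-14% | 12-12.3% | not run | 4.8% |
| 50% | 0.5 | 9.0-9.3% | 8.8-9.0% | not run | 4.8-4.9% |
| 20% | 0.5 | 6.4% | 5.7% | not run | 5.0% |

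**Boundary cases** (250 to 400 trials each, simulation error about 1-3 percentage points):
- Loss of 60% against 40%, unrelated to score: bias about 0, rejection 6-7%. Unequal loss alone creates no effect.
- Dropout in one arm depending on the unseen post-test score: independence GEE +2.0 to +4.1 points (17-60% rejection); exchangeable GEE +1.3 to +2.7 points (14-34%); baseline-adjusted +1.3 to +2.7 points (13-35%).

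**The case against.** The strongest reply is that the plan has left a setting open, not chosen an invalid analysis. In the baseline-dependent scenario an exchangeable GEE is nearly unbiased, so a reader who infers that the planned GEE is invalid goes further than the documents allow. This stands. Two limits apply: the simulated correlations were equal across visits, which suits that structure exactly, and the plan does not commit to it.

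Second, the t-tests do not decide effectiveness; section 3.10.2 and Table 3.4 give that to the GEE interaction. This stands too, so the t-test error rates concern supporting comparisons. That the t-tests use completers only and that the GEE is unweighted are inferences from silence, and an undeclared imputation cannot be ruled out.

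Third, a reader might infer that dropout is likely to differ by arm because only the intervention arm has sessions to complete before the first post-test. The documents do not show this. The burden is four sessions of about 10 minutes with reminders (3.7.2.2), both arms are evaluated with the same questionnaires (3.7.2.3), and waitlisted controls may have reason to stay.

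Fourth, a reader might infer that any bias would favour the intervention. The sign in the simulations comes only from letting low scorers leave the intervention arm. If high scorers left instead, the bias would reverse and could hide a real effect.

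**Conclusion.** The concern holds in a conditional form. The plan allows for heavy loss and claims intention to treat, but it does not specify an analysis whose validity under that loss can be judged. If dropout relates to literacy differently in the two arms, the completer t-tests and an independence-structure GEE are biased, in either direction. Under the stated assumptions the size is about 0.25 SD with 17-20% false rejection at 50% loss, and about 0.17 SD with 12-14% at the 33% loss that the inflation actually covers. With a weaker link (slope 0.5, 50% loss) rejection is about 9%, and it shrinks further as loss falls.

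These figures rest on an assumed correlation and assumed dropout slopes. They show what could happen and are not a forecast. Exchangeable GEE and baseline-adjusted analyses hold at about 5-6% when dropout depends on the observed baseline at 50% loss. Neither an exchangeable GEE nor a mixed model fully removes the bias when dropout depends on unseen scores: for a participant lost before the first post-test, the baseline is the only score available to any model. That is why a sensitivity analysis is needed as well as a better primary model.

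**What to change.** - Define intention to treat as all randomised participants analysed in their allocated arm.
- Make the primary analysis a likelihood-based repeated-measures mixed model (REML, unstructured covariance, SPSS MIXED), with baseline as a response and arm means constrained equal at baseline. It is valid under missing at random. Multiple imputation, or a GEE with a named non-independence working correlation, is an acceptable alternative. Whichever is chosen must be fixed before outcomes are seen.
- Report loss by arm and visit, and the baseline scores of dropouts by arm.
- Add one sensitivity analysis: multiple imputation with the imputed intervention-arm scores lowered in steps, for example 0.1 to 0.5 SD, until the conclusion changes.
- Label the t-tests (or rank tests) as descriptive completer summaries.

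The cost is SAP wording and a little more analysis in the same software. Recruitment, visits and questionnaires do not change.

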**Table 3.4 Summary of Statistical Tests**

| Objectives                                                                           | Statistical Tests        |
|---------------------------------------------------------------------------------------------|---------------------------------|
| Sociodemographic                                                                     | Chi-Square                      |
| Baseline Mental Health Literacy and Help-Seeking Behavior                            | Independent t-test              |
| Post Intervention Mental Health Literacy and Help-Seeking (within group difference)  | Paired t-test                   |
| Post Intervention Mental Health Literacy and Help Seeking (between group difference) | Independent t-test              |
| Effect of Health Education Intervention                                              | Generalized Estimating Equation |

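### Judged normality chooses between t-tests and rank tests for the unadjusted comparisons under objective 3, while Table 3.4 lists only t-tests; the effectiveness conclusion from the GEE is not affected

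*Combined protocol and SAP*

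**What the plan says.** Section 3.10.1 (Descriptive Analysis) checks normality by histogram, "Kolmogorov-Smirnov, and Shapiro-Wilk normality test". It gives no significance level and no rule for when the three checks disagree. It does not say what is tested: raw scores, changes or residuals, by arm or pooled.

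Section 3.10.2 (Inferential Analysis) makes each simple comparison conditional. Between groups, "if data were assumed to be normally distributed data, parametric tests such as Independent t-test will be utilized"; otherwise "non-parametric tests such as the Mann Whitney U test will be utilized". Within groups the paired t-test applies, or, for data judged non-normal, "non-parametric tests such Wilcoxon Signed Ranks test will utilize".

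Table 3.4 gives one test per row. The within-group row has the paired t-test. The row beginning "Post Intervention Mental Health Literacy and Help Seeking (between group difference" has the independent t-test. No rank test appears in the table.

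The treatment effect itself has a separate analysis, a covariate-adjusted GEE: "The effectiveness of the intervention will be based on the trial group and timepoint interaction result". Table 3.4 gives it its own row.

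**The concern.** A t-test compares means. A Mann-Whitney test compares distributions by rank and gives no effect in scale points. When the sample decides which is used, the hypothesis tested is not fixed before the data are seen, and one run of this trial could report a different quantity from another. Objective 3 (section 1.5.2) and both hypotheses (section 1.6) are worded as within- and between-group differences, so these comparisons answer stated objectives. Section 3.4.9 sizes the trial on a difference in means, which a rank test does not estimate.

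There is also an error-rate question. If the true means are equal but the arms differ in spread or shape, a rank test can reject more often than 5% as a test of equal means. A rule that switches to it inherits that error. Finally, sections 3.10.2 and Table 3.4 disagree on whether the t-test is fixed or conditional.

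**Working it through.** **Inputs from the plan.** Table 3.1 takes means of 75.91 and 69.02 and SDs of 8.13 and 8.23 (239 and 263 participants) from a published school-based trial. Alpha is 0.05 two-sided. Planned arm sizes are 44 before and 66 after the allowance for loss. A 50% loss from 66 leaves 66 × 0.5 = 33.

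**The plan's own figures.** The difference is 75.91 − 69.02 = 6.89. The pooled SD is √[(238 × 8.13² + 262 × 8.23²) / 500] = 8.18, as stated. The printed formula gives 2 × (8.18 × 2.80 / 6.89)² = 22.1 per arm, so the stated 44 per arm does not reproduce (44.2 is the total for two arms). That is a separate matter. What counts here is that the target is a mean difference and that the only SD ratio in the documents is 8.13 / 8.23 = 0.99.

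**Assumed for the simulation, because the plan gives none of it.** Shapiro-Wilk is applied at 5% in each arm, with Mann-Whitney if either arm rejects and the t-test otherwise. Arms are equal in size (33, 44 or 66) and means are equal. Skewed scores are reversed gamma with shape 4 (skewness −2/√4 = −1) or shape 2 (−2/√2 = −1.4).

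**How often the rule switches.** With truly normal scores, about 10% of trials (1 − 0.95² = 9.75%). At skewness −1, about 73-74% at 33 per arm, 86% at 44 and 97% at 66.

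**Between-group type I error for equal means, 33 to 66 per arm.**

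| Ratio of SDs between arms | Two-stage rule | t-test |
|---|---|---|
| 0.99 (skewness −1 and −1.4) | 4.9-5.5% | about 5% |
| 0.9 (both) | 5.2-6.2% | about 5% |
| 0.8 (both) | 5.8-8.0% | about 5% |
| 0.6, skewness −1 | about 8-11% | about 5% |
| 0.6, skewness −1.4 | about 11-19% | about 5% |

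These come from 4,000 trials per case. The Monte Carlo standard error is √(0.05 × 0.95 / 4000) = 0.3 points near 5%, and √(0.19 × 0.81 / 4000) = 0.6 points near 19%.

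**Other shapes.** With identical distributions in both arms (normal, skewed, heavy-tailed or truncated at a ceiling), the two-stage error was 4.7-5.5%. With equal means and SDs but different shapes, it was 6.2-7.2% for normal against left-skewed and 9.9-15.8% for opposite skews. The t-test gave 4.7-5.4% in those cases.

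**Within groups, mean change zero.** For differences with skewness of size 1, the paired two-stage rule rejected in 7.6-10.1% of samples, against 5.2-5.4% for the paired t-test. For exponential differences the figures were 17.0-27.5% and 6.4-7.5%, so the t-test is not exact there either, but it is much closer.

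**The case against.** The strongest reply is that the conclusion on effectiveness does not pass through the switch. It rests on the GEE interaction, which has no normality condition and adjusts for covariates. A reader might infer that the trial's main result carries an inflated error rate. The documents do not support that: only the unadjusted supporting comparisons are conditional.

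A second reply is that the link between the sections is partly inferred. The normality checks stand under the descriptive heading, and section 3.10.2 speaks of assumed normality without naming a test. This is fair. But no other criterion is given, so the checks in 3.10.1 are the natural basis for the choice.

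Third, the error inflation depends on inputs outside the documents. The two SDs in Table 3.1 are almost equal, and at that ratio the error is nominal. No skewness or ceiling is stated for the literacy scale. A ceiling strong enough to compress one arm's spread would usually also raise its mean, so it does not match a null of equal means. A reader might infer that inflation is expected; only its possibility is shown.

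Fourth, it is tempting to quote how often one arm passes Shapiro-Wilk and the other fails as the chance that the arms get different within-group tests. At skewness −1 that is roughly half of trials at 33 per arm and 29-30% at 66. Those rates concern raw scores in each arm, whereas a paired test concerns differences, so they do not measure that chance. Different tests in the two arms remain possible.

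What survives is that the reported quantity is left to the sample, that the text and the table conflict, and that the switch gave no useful protection in the between-group cases tried, where the t-test already held about 5%.

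**Conclusion.** The concern holds for the unadjusted within- and between-group comparisons under objective 3 and both hypotheses, and no further. Section 3.10.2 lets judged normality decide whether a mean difference or a rank comparison is reported, and Table 3.4 contradicts it by listing t-tests alone. The GEE conclusion is unaffected.

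Between-group error stays near 5% when the arms share shape and spread. It rises to about 6-8% at an SD ratio of 0.8 and 8-19% at 0.6, given equal means, skewness of −1 to −1.4 and the assumed switching rule; all of these are assumptions. The more certain harm is to interpretation: even with exactly normal scores, about one trial in ten would switch under that rule. This is a worthwhile improvement at almost no cost, not a threat to the trial's validity.

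**What to change.** Delete the normality-conditional sentences in section 3.10.2 and bring that section and Table 3.4 into agreement. For each outcome and each follow-up (2 weeks and 1 month), report the between-group mean difference with its 95% CI from the GEE already planned, or from a linear model adjusted for the baseline score with robust standard errors. Name one of the two in advance. Take the within-group mean changes from the same model. Do this whatever the normality checks show.

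Keep histograms as description. If a rank test is wanted, list it as a labelled sensitivity analysis that does not replace the mean difference.

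The cost is SAP wording. The downside is one extra sensitivity analysis to report.

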#### **3.10.2 Inferential Analysis**

The outcome variable will be compared at the baseline and post-test. For within-group difference, if data were assuming normally distributed data, parametric tests such as Paired t-

test will be utilized. But if data were assuming to be non-normal distributed data, non-parametric tests such Wilcoxon Signed Ranks test will utilize. For between groups difference, if data were assumed to be normally distributed data, parametric tests such as Independent t-test will be utilized. But if data were assuming to be non-normally distributed data, non-parametric tests such as the Mann Whitney U test will be utilized. Chi-Square test and Fisher Exact will be used to test the association between two categorical variables.

Multivariable analysis was done using generalized estimating equations (GEE) to determine the effect of the intervention on the primary and secondary outcome after adjusting for the covariates. The effectiveness of the intervention will be based on the trial group and timepoint interaction result. The effect of the intervention on changes in outcome measures will be determined after the intervention period. A summary of the statistical tests that will be used in this study can be found in Table 3.4.

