### 3.5 Study Variables

#### 3.5.1 Dependent Variables

The primary outcome for this study is mental health literacy, and the secondary outcome is help-seeking behaviour. Both the primary and secondary outcomes will be measured at baseline, 2 weeks post-intervention and, 1 month follow-up.

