#### 3.5.3 Covariates

The covariates for this study are socio-demographic factors such as age, gender, ethnicity, and household income level.

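### The group-by-time interaction is a change-score contrast: the baseline score is not named as a covariate, which costs (1 − rho)/2 of the attainable precision, with rho not given

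*Combined protocol and SAP*

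**What the plan says.** Section 3.5.1 sets the schedule: "Both the primary and secondary outcomes will be measured at baseline, 2 weeks post-intervention and, 1 month follow-up". Hypothesis 1 in section 1.6 also counts baseline among the time points for mental health literacy.

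Section 3.10.2 plans a GEE, adjusted for covariates, for the primary and secondary outcomes. On how success is decided it says: "The effectiveness of the intervention will be based on the trial group and timepoint interaction result". The next sentence frames the effect in terms of change in the outcomes.

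Section 3.5.3 lists what the model adjusts for: "The covariates for this study are socio-demographic factors such as age, gender, ethnicity, and household income level". The outcome's baseline score is not named there, in section 3.10.2 or in Table 3.4. For the post-intervention between-group comparison, Table 3.4 lists an independent t-test, which makes no use of baseline.

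The plan does not state outright that baseline is an outcome time point in the GEE. It names no working correlation structure and gives no correlation between baseline and follow-up.

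**The concern.** If baseline is one outcome time point among three and the arms may differ freely there, the interaction coefficient at a follow-up visit is the between-arm difference at that visit minus the between-arm difference at baseline. Randomisation makes the baseline means equal in expectation, so the full baseline difference that is subtracted is chance. Regression on baseline removes only the share of it that predicts follow-up. The change score removes all of it, which over-corrects when rho is below 1.

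The named covariates are unlikely to make up for this. Section 3.1 describes applicants as 18 or 19 years old, so age hardly varies, and a person's own earlier score would usually predict the later one better than demographics do.

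At stake are the width of the confidence intervals for both outcomes, and power if the effect is smaller than planned, in a trial that budgets for losing half its participants.

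The other reading also needs attention. If only the two follow-up visits were modelled, the interaction would test whether the effect differs between 2 weeks and 1 month, not whether there is an effect.

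**Working it through.** **Inputs.** From section 3.4.9: z = "1.96 (confidence level of 95"%) and z = "0.84 (power of 80"%). From Table 3.1: means 75.91 and 69.02, so a difference of 6.89, and pooled SD 8.18. The final size is stated as "After considering 50% loss to follow up, a final sample size of 132 (66 participants per arm"); half of 66 leaves 33 evaluable per arm. Rho is an assumption throughout.

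**The plan's own figure.** The size was "calculated by using the two population mean formula for hypothesis testing". With the plan's inputs:

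2 × 8.18² × (1.96 + 0.84)² / 6.89² = 22.1 per arm, or 44.2 in total.

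The stated "44 participants per arm" therefore matches the formula's total, not its per-arm number. That is a separate matter. What counts here is that the formula has no rho term, so the plan's arithmetic does not fix the precision of either analysis.

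**Variances.** Assume equal SD at baseline and follow-up, and work in units of SD² per arm:
- raw post-test comparison: 1
- change score: 2(1 − rho)
- baseline-adjusted: 1 − rho²

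Adjusted over change is (1 − rho²) / [2(1 − rho)] = (1 + rho)/2. The precision lost by the change score is 1 − (1 + rho)/2 = (1 − rho)/2. The adjusted standard error is smaller by 1 − √[(1 + rho)/2].

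| rho (assumed) | change | adjusted | precision lost | SE reduction |
|---|---|---|---|---|
| 0.3 | 1.40 | 0.91 | 35% | 19% |
| 0.5 | 1.00 | 0.75 | 25% | 13% |
| 0.6 | 0.80 | 0.64 | 20% | 11% |
| 0.7 | 0.60 | 0.51 | 15% | 8% |
| 0.9 | 0.20 | 0.19 | 5% | 3% |

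Against the raw post-test t-test, adjustment reduces variance by rho²: 25%, 36% and 49% at rho 0.5, 0.6 and 0.7.

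**Is the interaction really a change score?** In 600 simulated trials per rho value (44 per arm, three time points, complete data, exchangeable GEE without covariates), the interaction coefficient equalled the difference in mean change to rounding error. The simulated loss against baseline adjustment was 30% at rho 0.5 and 16% at rho 0.7, against 25% and 15% from the formula.

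**Power with 33 per arm.** Φ(difference / [8.18 × √(2v/33)] − 1.96), where v is the variance from the table. The difference of 4 is an illustrative smaller effect.

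| rho | 6.89: change v adjusted | 4: change v adjusted |
|---|---|---|
| 0.5 | 92.8% v 97.7% | 51.1% v 63.1% |
| 0.6 | 96.9% v 99.0% | 60.3% v 69.9% |
| 0.7 | 99.3% v 99.8% | 72.7% v 79.4% |

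**A hint at rho.** Table 2.5 gives 5.693 (4.682, 6.704) for the planning study without saying what it is. If it is a 95% interval for a baseline-adjusted or change-based group difference, the SE is (6.704 − 4.682)/(2 × 1.96) = 0.516. The unadjusted SE is 8.18 × √(1/239 + 1/263) = 0.731, so the variance ratio is 0.498. Then rho is √(1 − 0.498) = 0.71 (adjusted) or 1 − 0.498/2 = 0.75 (change), and the loss is 15% or 12%. That study used a different questionnaire, so this is only suggestive.

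**The case against.** **Power is ample in either case.** At the planning difference every figure above exceeds the planned 80%. This stands, and it limits the consequence. It does not remove the gain. The planning difference comes from a school programme of two 90-minute sessions in pupils with a mean age of 13 (Tables 2.3 and 2.4), measured with its own questionnaire. This trial uses the MHLS and four web sessions of about 10 minutes, so a smaller effect is plausible. Help-seeking has no sample-size calculation at all.

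**The planned contrast already uses baseline.** This also stands. A reader might infer that the plan ignores baseline altogether, but on the natural reading the interaction subtracts it. What is missing is regression adjustment, or a constraint to equal baseline means. Only the post-intervention t-test leaves baseline out.

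**The model is partly inferred.** Section 3.10.2 does not spell out the time points, and the wording of section 3.5.3 leaves the covariate list open. True, but a baseline literacy or help-seeking score is not a socio-demographic factor, and both readings of the interaction need the same repair.

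**The contrast is valid.** It is. A reader might infer bias from regression to the mean. Over repeated randomisations there is none; the over-correction concerns a chance baseline imbalance within one trial.

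**Conclusion.** The point holds as a loss of efficiency. On the natural reading, effectiveness is judged on a difference in change scores, which has (1 + rho)/2 of the precision of a baseline-adjusted comparison. The loss is 15% to 25% for rho between 0.7 and 0.5, or about 8% to 13% on the standard-error scale. It runs from 5% to 35% for rho between 0.9 and 0.3.

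These sizes rest on an assumed rho and on equal variances at baseline and follow-up. A reader might take 15–25% as a property of this trial; the documents give no rho, so it is not. Nor do they support a claim that this choice leaves the trial underpowered: at the planning difference with 33 per arm, power is about 93% even at rho 0.5. The practical gain is a narrower interval at every effect size, and roughly 7 to 12 points of power if the true difference were nearer 4. Since it costs nothing, the change should be made.

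**What to change.** In section 3.10.2, define the primary model as a GEE of the 2-week and 1-month scores with group, time, group × time, the baseline score of the same outcome and the demographic covariates. Do the same for help-seeking, and add the baseline score to section 3.5.3 and Table 3.4.

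Judge effectiveness on the adjusted between-group difference with its 95% confidence interval at each visit. It should not rest on the interaction term alone, which in a follow-up-only model tests only whether the effect differs between visits.

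State the working correlation. If baseline is instead kept as an outcome with the arm means constrained equal, it must not be independence; exchangeable or unstructured would serve. Under independence the constrained estimate reduces to the raw post-test difference. In 300 simulated trials (33 per arm, rho 0.6, complete data) its SE was 0.246 SD, worse than the change contrast at 0.207. With an exchangeable structure it was 0.190, against 0.191 for regression on baseline.

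The cost is analysis-plan wording only. The baseline scores are already to be collected, and the planned software can fit the model.
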